### Assignment for intervention

#### Allocation

Consenting participants will be randomised by computer-generated online block randomisation to either group 1 (IBD nurse CONSULT + BOOKLET) or group 2 (BOOKLET alone), stratified by centre and presence/absence of an ileo-anal pouch (which is associated with a high rate of FI), and using randomised blocks of two, four or six. Randomisation will be designed and managed by the PCTU.

#### Blinding

Participating centres will be blinded to sequence allocation until they log into the system and confirm participant eligibility. Blinding of participants and IBD nurses is not possible. The trial statistician will be blinded to treatment allocation during data analysis. We have not specified any permissible circumstances for unblinding in this low-risk trial.

### Data collection, management and analysis

#### Data collection

Data will be collected by a self-completed booklet of questionnaires. Study outcome measures will be recorded at baseline (booklet contains 19 printed pages) and at 6 months after randomisation (booklet contains 26 printed pages as it includes study-specific outcome tools and health economic data). Acceptability of these outcome booklets has been verified by our Patient and Public Involvement (PPI) Group. Preliminary piloting has found these take 20–30 minutes to complete and our four PPI representatives have commented that this is not unduly burdensome. Six months after randomisation, the outcome measures will be sent by post with two postal reminders for non-responders after 3 and 5 weeks.

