### Trial design

This is a two-arm parallel group randomised controlled trial (RCT) with 1:1 allocation intended to show superiority of IBD nurse intervention plus an information booklet, compared with an information booklet alone. The study has a total duration of 30 months.

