### Sample size for the trial

Sample size is based on a published response (improvement) rate for conservative intervention for FI and a difference of 3 points in the St Mark’s FI score at 6 months being considered to be of clinical significance to people with FI but without IBD [23]. We will aim to randomise 186 people, with anticipated drop-out of 20 % (based on our previous intervention studies and clinical experience), which will be sufficient to detect a difference of 3 points on the St Mark’s scale assuming a standard deviation of 5, with a power of 90 %, using a 5 % significance level (74 needed per arm, increased to 93 to allow for drop-outs).

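### A sheet with only the St Mark's score, enclosed with the last postal reminder, could save some primary outcomes that are lost when the 26-page booklet is not returned

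*Protocol article*

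**What the plan says.** The Data collection section sets the 6-month procedure: "the outcome measures will be sent by post with two postal reminders for non-responders after 3 and 5 weeks". No telephone, e-mail, clinic or short-form route is described. The same section explains that the 6-month "booklet contains 26 printed pages as it includes study-specific outcome tools and health economic data"; the baseline booklet has 19 pages. Piloting put completion at 20–30 minutes, and the four patient representatives found that acceptable.

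The primary outcome is the St Mark's score (0–24) at 6 months (Primary outcome measure). Outcomes are recorded at baseline and 6 months only, with no later follow-up (Data management). The intention-to-treat analysis takes every participant who has outcome data, and adjusts for the baseline value, centre and ileo-anal pouch (Statistical methods).

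The sample size section allows for "anticipated drop-out of 20"% by raising 74 per arm: "increased to 93 to allow for drop-outs".

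The Study outcome measures section says a research nurse gives the booklet to the participant. That may describe baseline only. The Data collection section is explicit about 6 months, so I work from it, but the two statements should be reconciled.

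**The concern.** There is no intermediate score to fall back on. When a booklet does not come back, a randomised participant leaves the primary analysis, although the score needed is only part of what was posted. The protocol itself attributes the length of the 6-month booklet to study-specific tools and health economic questions, not to the primary outcome.

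Participants know their allocation (Blinding), and the two arms do not have the same reasons to reply. Under Post-trial care, booklet-only participants are offered the nurse intervention once the 6-month questionnaires are completed, subject to local capacity. The nurse arm has no such inducement, but it has had more contact with staff. The direction of any imbalance is therefore unknown, but imbalance is plausible. A larger sample does not remove bias from selective non-response; a smaller share of unknown outcomes limits it.

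**Working it through.** **Inputs from the protocol.** A "two-arm parallel group randomised controlled trial (RCT) with 1:1 allocation"; 186 randomised (93 per arm); 20% drop-out; a sample described as "sufficient to detect a difference of 3 points on the St Mark’s scale assuming a standard deviation of 5"; power 90%; significance level 5%. I take the test as two-sided, which is not stated.

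**The plan's own figures.** The drop-out step reproduces: 74/(1 − 0.20) = 92.5, so 93 per arm and 186 in total. The 74 does not: 2 × [5 × (1.96 + 1.2816)/3]² = 58.4, so 59 per arm. It would follow if 20% had already been added once (59/0.80 = 73.75, so 74) or if power were 95% with a t-test (73.2, so 74). That is a separate matter. Here it matters only because it leaves the trial with spare power.

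**Expected loss.** 186 × 0.20 = 37.2 participants, leaving 148.8 scores (74.4 per arm).

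**Assumptions.** The documents give no recovery rate, so I assume that 25% or 50% of non-returners send back the sheet. Nor do they divide the 20% into withdrawal and non-return, so I take non-return as all of it or half of it. The standard error scales as 1/√n.

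| Non-return as share of the 20% | Recovery | Scores gained | Total scores | Loss | SE relative to plan |
|---|---|---|---|---|---|
| all (37.2) | 25% | 9.3 | 158.1 | 15% | √(148.8/158.1) = 0.970 |
| all (37.2) | 50% | 18.6 | 167.4 | 10% | √(148.8/167.4) = 0.943 |
| half (18.6) | 25% | 4.65 | 153.45 | 17.5% | √(148.8/153.45) = 0.985 |
| half (18.6) | 50% | 9.3 | 158.1 | 15% | 0.970 |

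**Confidence interval.** The 95% half-width is 1.96 × 5 × √(2/n per arm). It is 1.61 points at 74.4 per arm and 1.52 at 83.7, the best case above.

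**Power (normal approximation, 3 points, SD 5).** 95.5% at 20% loss, 96.5% at 15% and 97.3% at 10%. Because 59–60 per arm suffice for 90%, that power survives a loss of 1 − 60/93 = 35% to 1 − 59/93 = 37%.

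**Bias, for illustration only.** With equal loss in both arms, bias = share lost × (effect in those observed − effect in those missing). Suppose the effect is 3 points in those observed and 0 in those missing. The bias is then 0.20 × 3 = 0.60 points. It falls to 0.15 × 3 = 0.45 or 0.10 × 3 = 0.30 if those recovered resemble those still missing. If those recovered resemble ordinary responders instead, and the missing group as a whole still averages 0, the remainder carry the whole gap. At 50% recovery that gap is 6 points, and 0.10 × 6 = 0.60: no reduction.

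**The case against.** The strongest reply is that nothing here is misstated. Two postal reminders are a definite procedure, a short form is an optional extra, and a journal article need not list what each reminder contains. That stands, and it limits the point to an improvement.

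Several stronger readings are tempting, and the protocol does not support them:

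- **That anyone who will not finish 26 pages is lost.** The analysis needs outcome data, not a complete booklet. On its face, a partly filled booklet with the St Mark's items answered counts. Only non-return, or return without those items, loses the score.
- **That length causes non-return.** The only evidence on burden is favourable. It is thin (preliminary piloting and four representatives), but it does not show the opposite.
- **That the plan only over-recruits and does nothing to limit loss.** It has reminders and patient review of the booklets, and it tries to keep people who stop the intervention in data collection. The post-trial offer may also encourage return in the booklet arm.
- **That the 20% is recoverable.** It is general drop-out, based on earlier studies and clinical experience. People who withdraw completely cannot be recovered by a mailing.
- **That the trial would be short of power.** At SD 5 it would not. Power would matter only with a larger SD: at SD 6 it is 86% at 20% loss and 90% at 10%.
- **That trying costs nothing.** Some people who would have returned the full booklet may send the sheet instead, even if no extra primary score is gained.

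**Conclusion.** The point holds as a low-cost improvement. The protocol describes only postal pursuit of a 26-page booklet and mentions no reduced version. With one post-baseline time point and an analysis of those with data, each unreturned booklet is a lost primary outcome.

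A St Mark's-only sheet could recover about 9–19 scores if all drop-out is non-return, or about 5–9 if half is. Loss would fall from 20% to somewhere between 17.5% and 10%, and the standard error by roughly 1.5–6%. These figures rest on an assumed 25–50% recovery; the true rate could be lower, including zero.

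The benefit is a smaller share of unknown outcomes in an unblinded trial, with a modest gain in precision. Any fall in bias is illustrative, because it depends on an assumed 3-point gap and on those recovered resembling those still missing.

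**What to change.** At the 5-week reminder, enclose in both arms a single sheet with the St Mark's score only, worded exactly as in the booklet. The covering note should still ask for the full booklet but say that the sheet alone is useful. I assume the items fit on one sheet.

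Include these scores in the primary analysis. Baseline score, centre and pouch status are collected at or before randomisation, so the sheet supplies the one missing value. Flag each sheet score and its completion date, and report a sensitivity analysis without the sheet scores. If the St Mark's items are not already at the front of the 6-month booklet (the order is not stated), placing them there would help with partial completion.

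The cost is one printed sheet per remaining non-responder and a minor notification to the ethics committee; the documents give no cost figure. The real downside is that some late responders may send only the sheet, so their secondary and economic data are lost. Offering it only at the last reminder limits this. On the dates under Trial status, recruitment opened on 11 May 2015, so the first 6-month mailings fell due around November 2015, after this article appeared. The change could have covered nearly all participants.

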#### Data management

Electronic study data will be pseudonymised, stored on a secure server and accessed via a secure network. Access is restricted to authorised personnel only and via secure, password-controlled, role-based access. All identifiable data stored in paper files will be managed securely in restricted-access, lockable containers at the individual participating sites. All authors will have full access to the final dataset. Following study closure, all data and study documentation will be archived at the sponsor site and held for 10 years, in accordance with sponsor requirements.

The PCTU standard operating procedures for data entry, quality control, data extraction and database freeze will be followed, and are available on request. All outcome measures are self-reported and will be returned to the recruitment site for inputting by the trial manager. The data management plan (available on request from the lead author), which includes source data verification and instructions for data storage, will be followed. After data cleaning, the database will be frozen and analysed by the study statistician, who will be blinded as to group allocation.

Outcome measures (see above) will be recorded at baseline and at 6 months following randomisation. There will be no additional follow-up. The study endpoint will be the date of database lock following data inputting, cleaning and checking. There will be no further quantitative data collection after this point.

#### Statistical methods

Primary and secondary outcome measures at baseline along with recruitment rates, session attendance, and withdrawal from the intervention will be presented as means and standard deviation for approximately normally distributed continuous variables, medians and interquartile ranges for non-normally distributed variables, and frequencies and percentages for categorical variables. Estimates of treatment effect on primary and secondary outcomes at the follow-up assessments will use an intention-to-treat (ITT) framework, implemented using a regression model, adjusting for baseline values of the outcome, centre, and presence of an ileo-anal pouch. ITT analysis will include all participants with outcome data regardless of adherence to the intervention. Where participants wish to withdraw from the intervention, we will attempt to retain them in the data collection, unless they express a wish to be withdrawn completely.

Also reported:Comparison between the groups on secondary outcome measures, although the study is not powered to detect significant differences.Sub-group analysis, including any apparent difference in response according to type of IBD (Crohn’s vs. other forms of IBD), childbirth (any vaginal delivery vs. none)The impact of experiencing disease flare-up (defined as needing to escalate or initiate medication doses) on benefits of interventionHealth economic analysis (below)Process data from study-specific questionnaire and IBD nurse records on which interventions were usedQualitative data (see below)

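### Flare-up arises after randomisation, so the planned analysis of how it affects the benefit of the intervention is not a randomised comparison and should be descriptive

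*Protocol article*

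**What the plan says.** The protocol article, Statistical methods, lists several analyses to be reported besides the main comparison. One is a subgroup analysis, including "any apparent difference in response according to type of IBD" and by childbirth. The next, a separate item, is the effect of a disease flare-up on the benefit gained from the intervention. There, flare-up means that medication had to be started or stepped up.

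Four other places bear on this item:

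- Inclusion criteria: no flare-up at entry, with stable disease and treatment for the preceding 3 months.
- Secondary outcome measures: any IBD flare-up while the intervention was under way or afterwards, again defined by a medication change.
- Interventions: three to four 30-minute nurse sessions in group 1 only. Both groups get the booklet.
- Harms: flare-up as an expected adverse event, defined by a score of at least 5 on either disease activity index.

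The main model is a regression "adjusting for baseline values of the outcome, centre, and presence of an ileo-anal pouch". The article does not call the flare-up analysis descriptive or non-randomised.

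**The concern.** Type of IBD and childbirth are recorded before randomisation, so arms remain comparable within their categories. Flare-up is different. It happens after allocation, and allocation may influence both whether it happens and whether it is recorded. Sorting participants by flare-up can then put different kinds of patient in the nurse and booklet sides of each group, and a difference in apparent benefit may only reflect that sorting.

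At stake is a statement that nurse support helps less, or more, in people who flare. The Discussion expects the trial's work to inform how services are configured, so such a statement could influence who is offered the nurse sessions.

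**Working it through.** **Timing.** Nobody is in flare at entry (Inclusion criteria), and flare-up is counted during or after the intervention (Secondary outcome measures). The modifier therefore arises after randomisation.

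**Can the arm affect it?** Nurse contact exists in one arm only and could change symptoms, reporting or prescribing. The definition in Statistical methods names no drug class. Background and rationale puts diet and anti-diarrhoeal medication at the start of the stepwise approach, and Booklet development lists anti-diarrhoeals among the advice. Both arms receive that advice, so the route to imbalance is greater uptake with nurse support. Read literally, such a start counts as a flare-up.

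**Size.** The article gives no flare-up frequency and no link between severity and flare-up, so there is no figure to reproduce. Two inputs are the plan's own: the design is "sufficient to detect a difference of 3 points on the St Mark’s scale", "assuming a standard deviation of 5". Everything else is assumed:

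- U is latent severity (mean 0, SD 1) not captured by the baseline score.
- Score = constant − 3 × arm + 2.5 × U + noise, total SD 5. U then explains 2.5²/5² = 25% of the variance.
- Log-odds of flare-up = a + s × U + b × arm + c × U × arm.
- The true benefit is 3 points for everyone, so there is no modification by flare-up.

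The apparent effect in a flare group is −3 + 2.5 × (mean U in the nurse arm − mean U in the booklet arm, within that group). The means of U below come from numerical integration.

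1. *Arm does not affect flare-up (b = c = 0).* Mean U is equal across arms in each group, so the effect is −3 in both and there is no bias.
2. *Arm raises flare-up risk equally for all (s = 0.7, 22% in the booklet arm).*
   - Nurse arm 31%: flare group 2.5 × (0.440 − 0.504) = −0.16; no-flare group 2.5 × (−0.198 + 0.142) = −0.14.
   - Nurse arm 41%: flare group 2.5 × (0.373 − 0.504) = −0.33; no-flare group 2.5 × (−0.259 + 0.142) = −0.29.
   - Each within-group effect is off by about 0.1 to 0.3 points, but the two groups differ by less than 0.1. With s = 1, 24% in the booklet arm and 8% to 50% in the nurse arm, the groups differ by about 0.1 (0.05 to 0.16).
3. *Some anti-diarrhoeal starts recorded as flare-ups in the nurse arm.* Take s = 0.7 and 22% true flare-ups in both arms. Add 10% of nurse-arm non-flarers, irrespective of severity. Mean U among recorded nurse-arm flarers is (0.22 × 0.504 − 0.078 × 0.142)/(0.22 + 0.078) = 0.335, so the flare-group shift is 2.5 × (0.335 − 0.504) = −0.42. With 20%, the mean is (0.22 × 0.504 − 0.156 × 0.142)/0.376 = 0.236 and the shift is −0.67. The no-flare group does not move, so false modification is about 0.4 to 0.7 points.
4. *Arm changes which patients flare (s = 1, 24% in the booklet arm).*
   - c = −1, b = 0 (nurse arm 20%): flare group −3 + 2.5 × (0 − 0.653) = −4.63; no-flare group −3 + 2.5 × (0 + 0.203) = −2.49; difference about 2.1 points.
   - c = +1, b = 0.7 (nurse arm about 39%): flare group −3 + 2.5 × (0.739 − 0.653) = −2.79; no-flare group −3 + 2.5 × (−0.483 + 0.203) = −3.70; difference about 0.9 points.

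**Would an interaction term help?** No. An arm-by-flare coefficient estimates the between-group difference, so the false differences in cases 3 and 4 would appear in it. None of these errors shrinks with sample size. Similar flare-up frequencies do not give reassurance either: 24% against 20% in case 4 goes with the largest error.

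**The case against.** The item is supplementary and states no method. It does not say that arms will be compared within flare groups or that a causal claim will be made. In the mild case the shift is at most about a tenth of the 3-point difference (0.33/3 = 11%), and the larger figures need further assumptions. Secondary outcome measures speaks of an IBD flare-up, so medicines for IBD may be what is meant. Adjustment for the baseline score would absorb part of any severity difference. The intention-to-treat analysis already includes all participants with outcome data, whether or not they flare.

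Most of this stands, and it limits the point to one secondary item of uncertain size. It does not remove it. Any answer to how flare-up changes benefit must contrast the arms by flare status, and an unseen analysis plan cannot make that a randomised comparison. The definition as printed does not exclude anti-diarrhoeals.

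A reader might go further and infer that the subgroup wording, "any apparent difference in response according to type of IBD", is a rule under which chance differences between Crohn's disease and other IBD will be reported as real. With 74 evaluable per arm, an even split and 72% power in each half, exactly one half would be significant in 2 × 0.72 × 0.28 = 40% of trials. The article does not support that reading. It states no within-subgroup significance rule, the two factors have fixed categories recorded before randomisation, and the word apparent is hedged. The regression it describes is the main-effect model, where a subgroup term would not be expected. Interaction tests and exploratory labels are commonly left to the statistical analysis plan.

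**Conclusion.** The point holds for the flare-up item only. As worded, it treats an event after randomisation, which the arm can influence, as a modifier of benefit. The result cannot be read as the effect of flare-up on benefit, with or without an interaction term. The direction and size of the bias are unknown. Under the assumptions shown, within-group effects shift by about 0.1 to 0.3 points in the mild case with little false modification, and false modification of about 0.4 to 2.1 points is possible if the arm changes who is recorded as flaring. If the arm has no influence on flare-up, there is no such bias. The primary result is not touched, and the subgroup analyses by type of IBD and childbirth are not faulted.

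**What to change.** In Statistical methods, replace the flare-up item with three outputs: flare-up frequency by arm; the intention-to-treat effect regardless of flare-up; and scores by arm and flare status, shown descriptively and labelled non-randomised, with no conclusion about effect modification. Reconcile the flare-up definitions in Secondary outcome measures and Statistical methods (medication change) with that in Harms (index score), and state whether anti-diarrhoeal starts count.

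The cost is a few sentences. Data collection, sample size and primary analysis do not change. The downside is that the trial gives up a causal statement about flare-up and benefit.

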#### Health economic analysis

The health economics evaluation will estimate the costs associated with the delivery of the nurse-led FI management programme to patients with IBD, and compare the use of health care resources by patients receiving the two FI management interventions: (i) booklet plus nurse consultations and (ii) booklet alone. The analysis will be conducted from the perspective of the NHS and Personal Social Services. Economic evaluation methods will adhere, as far as possible, to the NICE Guide to the Methods of Technology Appraisal 2013 [30].

The cost of delivery of the nurse-led FI management programme will include: the cost of booklet development and production; the cost of training IBD nurses; the cost of consultations with IBD nurses. In addition to the cost of delivery of the FI management programme, the costs of health care services use by participants will be studied. These costs will cover primary care services including consultations, medication, investigations and referrals to secondary care. Secondary care services will include outpatient appointments, inpatient episodes and accident and emergency department (A&E) visits. A resource-use questionnaire asking participants about their use of health care services and medication has been developed using the online Database of Instruments for Resource Use Measurement [31]. Primary and secondary care unit costs will be derived from the UK Unit Costs of Health and Social Care [32]. The unit costs for secondary care will be based on the UK National Schedule of Reference Costs [33]. The unit costs for medication will be obtained from the Prescription Cost Analysis database [34]. Costs associated with the two FI management strategies will be presented in a disaggregated format with effectiveness outcomes (cost-consequences analysis). The estimated mean costs for each group will be presented alongside the mean estimates of primary and secondary outcomes.

